# **ABBREVIATIONS**

CC Cervical cancer

SVA Single Visit Approach

SAT Screen and Treat

LMIC Low and middle income countries

WHO World Health Organization

TA Thermal ablation

D&I Dissemination and Implementation

RE-AIM Reach, Effectiveness, Adoption, Implementation and Maintenance

RH Reproductive Health

NACC National Control Cancer Program

IDI In-depth Interviews

CFIR Consolidated Framework for Implementation Research

HPV Human Papilloma Virus

DHIS Demographic Health Information System

KNH Kenyatta National Hospital

LEEP Loop Electrosurgical Excision Procedure

VIA Visual Inspection with Acetic acid

VILI Visual Inspection with Lugol’s Iodine

IRB Institutional Review Board

KEMRI Kenya Medical Research Institute

CIN Cervical Intraepithelial Neoplasia

NIH National Institutes of Health (US)

HIV Human Immunodeficiency Virus

ORIC Organizational Readiness for Implementing Change

STI Sexually transmitted infection

PrEP Pre-exposure prophylaxis

IS Implementation Science

KMET Kisumu Medical and Educational Trust

US United States

UW University of Washington

VCT Voluntary counseling and testing

MoH Ministry of Health

PHRD Partners in Health and Research Development

KEMRI Kenya Medical Research Institute

ICRC International Clinical Research Centre

CME Continuous Medical Education

QA Quality Assurance

UoN University of Nairobi

TDABC Time-driven activity-based costing

# **EXECUTIVE SUMMARY**

Cervical cancer (CC) is almost entirely preventable with current technologies, yet, it remains the 4^th^ most common cause of cancer incidence and mortality among women globally.(1) CC is the most common cause of cancer and cancer deaths among women in Kenya, and 90% of CC deaths occur in low- and middle- income countries (LMIC).(2) To achieve the 2018 World Health Organization (WHO) call to action towards global CC elimination, there is an urgent need to adapt, implement, and scale-up effective technologies in LMICs.(3, 4)

The mainstay of CC prevention in LMIC has been the single-visit approach with screen-and-treat (SVA-SAT) method, using visual inspection with acetic acid (VIA) and ablative treatment with cryotherapy to manage precancerous lesions. It is a low-cost screening approach and minimizes loss to follow-up compared to traditional cytology.(5) Despite well-established evidence of the effectiveness of VIA on population-level reduction in CC burden,(6-8) the estimated screening uptake among women aged 30-49 in Kenya is 16%,(9) far below the WHO’s target of 70% and twice-lifetime screening of women ages 35-45 by 2030.(3) In Kenya, there is extremely low fidelity of SVA-SAT; up to 70% of screen-positive women do not receive treatment, demonstrating the science-practice gap.(10) The low treatment rate has been attributed to programmatic and logistical challenges of implementing cryotherapy in low-resource settings (e.g., equipment shortage, costs, supply chain difficulties of refrigerant gas, equipment failure, and treatment duration >10 min).(11-13) Thermal ablation (TA) is an effective alternative to cryotherapy for ablation of precancerous lesions, and has been recommended by the WHO since 2019.(14) Preliminary data from an investigative team member demonstrated safety, effectiveness, and acceptability to women when delivered by nurses in Zambia and Kenya.(15, 16) The portable device can be charged with electricity, batteries or solar panels, which is ideal for low-resource settings.(17) Successful implementation and scale-up of TA within the SVA-SAT approach could optimize CC prevention.

Testing dissemination and implementation (D&I) models to achieve population-based CC prevention is a top priority in Kenya’s National Cancer Control Strategy.(18) A context-informed scale-up of the SVA-SAT+TA in reproductive health (RH) clinics will be essential to achieve this goal. We have assembled a multidisciplinary team, including the head of the Division of National Control Cancer Program (NCCP) and TA experts, to advance the pragmatic delivery of SVA-SAT+TA. We propose a five-year prospective, stepped-wedge, cluster randomized trial to implement SVA-SAT+TA in 10 reproductive health (RH) clinics in central Kenya. We will use mixed-methods evaluation based on the RE-AIM (Reach, Effectiveness, Adoption, Implementation and Maintenance) framework to assess the intervention’s impact. We will collaborate with multi-level (clinic, county, national) stakeholders to develop a sustainable D&I strategy and leverage trial implementation to include costing and budget impact analysis. Our objective is to develop and evaluate a locally contextualized dissemination and implementation (D&I) strategy for SVA-SAT with TA (SVA-SAT+TA) to inform national scale-up. Our hypothesis is that TA will enhance the feasibility, adoption, and sustainability of CC prevention services via SVA-SAT, compared to the standard of care with cryotherapy.

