**Table 2: Comparing Cryotherapy and Thermal Ablation**

**Kenya National Cervical Cancer program (NCCP) is committed to cervical cancer prevention.** Kenya 2017-2022 national cancer control strategy has identified prevention, screening and early detection as the first of five strategic objectives to cancer control.(34) The 2018 cervical cancer screening guidelines propose to have every woman age 25-49 screened regularly for cervical cancer.(35) Despite the well-established evidence on the effectiveness of VIA on the population-level reduction in cervical cancer burden, the screening coverage and treatment of screen positive lesions remain low.(36) In an effort to expand screening coverage the Kenya NCCP has an on-going pilot project, which is field testing HPV testing for screening in six counties in Kenya. Concurrently, the NCCP is conducting a survey in public facilities to assess equipment coverage for cervical cancer control services. Over the last two decades various projects have introduced screening and treatment equipment to public health facilities, but the services often cease once the project ends. In Kenya, the gap that exists is between the decision to adopt an intervention (cervical cancer prevention policy and guidelines) and the routine use of interventions (VIA and cryotherapy). The lack of intervention uptake is reflected on inadequately skilled providers at RH clinics, inconsistent use of cryotherapy following screening and lack of community awareness.(37) The barriers and facilitators of this inadequate uptake require further interrogation to inform a sustainable program. Preliminary discussions with health care providers providing services at 12 potential project RH clinics in central Kenya, revealed challenges consistently related to cryotherapy equipment and procurement of supplies. Among clinics surveyed with cryotherapy equipment, challenges included equipment failure, high cost of refrigerant gas, and high turnover of trained personnel. They reflect challenges identified in published literature.(26)

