**Clinic Study Setting:**

We will implement this work in ten health facilities in Embu, Kiambu, Nairobi and Murang’a counties in central Kenya, including urban faith-based , rural and urban health facilities (Table 3). Reproductive health services in the county are led by a county gynecologist and managed by reproductive health coordinator. In large health facilities, a resident gynecologist leads reproductive health services. Services in smaller health facilities are led by a clinical officer or nurse. Reproductive health services in Kenya are mostly offered by nurses. Selected facilities currently use VIA for CC screening, they screened 1237 women over a four month period with a positivity rate of 5% . This sample was purposively selected to be nationally representative and heterogeneous in terms of staffing and service.

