**Figure 3: Stepped Wedge Implementation**

***Randomization****:* Clinics will be randomly assigned to start intervention delivery at one of the three study steps, with clusters of 3-4 clinics per step; randomization of clinics to the order of intervention steps will be stratified by size and will take place at the stakeholder meeting, which will include participation of clinic personnel.

***Training phase****:* Before SVA-SAT + TA implementation, we shall train health providers in participating RH clinics on thermal ablation techniques, inclusive of refresher training on VIA/VILLI as part of single-visit-approach as per IARC guidelines.(66). The training curriculum will be adapted to address gaps identified during Aim 1. The research training team will provide in person, on-site hands-on training at each facility followed by technical support for a duration of one week. Each trainee will be assessed for proficiency, which will be determined through the observation of a preset number procedure and certified with a proficiency certificate. To create demand and provide an adequate number of clients for screening and demonstration of TA techniques, our team which has over 15 years of successful community engagement in this region, alongside RH clinic personnel will conduct outreach community activities prior to scheduled on-site training. The selected RH clinics have some of their providers trained on VIA/VILI and cryotherapy. Our team of investigators has three reproductive health experts with TA training skills ([name], [name], [name]) who will train trainer of trainers at each RH clinic. Training will be provided with engagement of the KMET cure-cancer program who will provide consultant training services for the trainer of trainers for the initial 2 clinics, thereafter, the research team, led by [name], together with the county trainer of trainers will provide on-site hands-on training. [name] (project-PI) and [name] are skilled in colposcopy, loop electrosurgical excision procedure (LEEP), cryotherapy and TA, with years of experience training health care providers in addition to providing cervical cancer clinical services, will lead HCP training. In addition to thermal ablation training, quarterly continuous medical education (CME) which will include refresher CMEs on cervical cancer prevention and refresher didactic training on VIA will be provided during implementation.

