**Power and sample size** According to data on cervical cancer screening and preventive treatment for Kiambu County from 2017-2019, 20% of cervical cancer screening clients who screened positive received cryotherapy or LEEP. Routine data from our proposed study facilities show an average of 30 clients per month were screened at each facility in the first three months of 2020 (**Table 3**), corresponding to approximately 10% of eligible clients. The primary effectiveness outcome is the proportion of screen-positive women who receive same day ablation treatment. Assuming six-month waves, 30 clients screened per month and a 5% screen positive rate, we will have an average of 9 screen-positive women per facility per wave. Assuming an intracluster correlation coefficient of 0.2, alpha=0.05 and 20% treatment coverage pre-intervention, we will have 80% power to detect a three-fold increase to 60% treatment coverage using thermal ablation (R (v 3.6.3) package swCRTDesign (v 3.1)). We estimate that 90% of screen positive women will be eligible for ablative treatment.(49)

**Data analysis**: The primary analysis of proportion of screen positive women who are treated pre vs post- intervention. We will use weighted least square methods appropriate for this facility-randomized three-wave step wedge design, where all clinics begin in the control condition, We will consider the intervention effect to be fixed throughout the exposed period, but random effects per facility and wave. To analyze secondary outcomes of increase in proportion of trained providers (the **REACH** outcome) and increase in number screen-positive (secondary outcome) we will use the same analysis approach for the binary and count outcome. Exploratory analysis will examine potential effect modification of facility-level factors such as patient volume, patient to provider ratio, and women screened. Potential multi-level adjustment variables include individual-level factors such as age and access to resources. The HPV sub-study in women treated with TA will assess HPV clearance in HPV-positive women. Assuming 70% of screen-positive women test positive for HPV prior to TA (N = 140), the confidence interval for HPV clearance will be +/-8.1%

- **ADOPTION**

Our primary outcomes for adoption will be

1. the proportion of clinics incorporating TA into routine care through updated policies
2. Proportion of trained providers performing SVA-SAT +TA for screen positive women and

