Working together with the clinical team at the implementing facilities, we will develop a clinic report form that supports comprehensive data collection for women receiving cervical prevention services. Research data will be extracted from these clinical records. The data on the research clinic report form will be designed to support completeness of reporting and it will reflect standard clinical care data. This form will remain in the participant records in the health facility. We will then abstract data from this record.

Data will be entered directly to a password protected tablet and uploaded to the data files at the PHRD clinical trial facility data room. The data system at the clinical trial facility are in compliance with human subject protection guidelines. There will be no name of personal identifiers abstracted from the patient clinical files.

Written informed consent will be required for (i) participants selected for HPV testing and follow up for a 6-month period to assess for HPV clearance (ii) all qualitative interviews. The informed consent process will be voluntary and without coercion. Request to participant in the study will be done within an environment that allows the prospective participant to be well informed and to understands the purpose of the study and the expected procedures involved in participation. The informed consent form will be read and explained, and those willing to consent to participate in the study will be asked to sign a paper copy of the consent form.

After obtaining informed consent, the study staff will conduct study procedures in a private area of the clinic. Eligible reproductive health clinics will be clinics that provide cervical cancer screening services, their frontline providers, clientele and managers. We will seek permission from facilities to abstract program data and individual patient demographics and medical data.

In addition, qualitative data on single visit cervical cancer screening and treatment with thermal ablation delivery process from individual and provider key informant interviews will be collected. Logs with participant identification data will be stored in a locked file cabinet and access to all electronic data will be restricted with password and encryption protection.

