**Potential Benefits**

Participants will receive individualized cervical cancer risk counseling, access to cervical cancer screening and treatment of pre-cancerous cervical lesions. Women who are diagnosed with pre-cancerous lesions of the cervix will be provided with access to onsite (unless the lesion is not amenable to ablative therapy), same visit treatment.

Participants and their communities may benefit in the future from information learned from this study. The selected reproductive health clinics will receive thermal ablation equipment, personnel will be trained, provided with certificates, receive continuous medical education on cervical cancer prevention procedures and techniques during the project period. This will increase individual clinical expertise, and facilities will be more attractive to clientele due to increased access to services for women in the catchment area.

The Kenya cancer prevention and control program will receive evidence-based data to inform delivery to scale of a costed strategy that can lead the country ahead of the curve towards achieving the global agenda of cervical cancer elimination.

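### The hypothesis credits thermal ablation over cryotherapy, but the design compares a supported SVA-SAT+TA package with existing practice, with or without working cryotherapy

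*Protocol*

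**What the plan says.** The Executive Summary contains two statements that do not match. The objective concerns a strategy: "Our objective is to develop and evaluate a locally contextualized dissemination and implementation (D&I) strategy for SVA-SAT with TA". The hypothesis that follows concerns the treatment device: "TA will enhance the feasibility, adoption, and sustainability of CC prevention services via SVA-SAT, compared to the standard of care with cryotherapy".

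On the comparator, Human Subjects Considerations states "Eligible reproductive health clinics will be clinics that provide cervical cancer screening services". Clinic Study Setting adds "Selected facilities currently use VIA for CC screening". Neither requires on-site treatment capacity. Background and Rationale reports discussions with providers at 12 potential clinics: "Among clinics surveyed with cryotherapy equipment, challenges included equipment failure, high cost of refrigerant gas, and high turnover of trained personnel". The Training phase paragraph says "The selected RH clinics have some of their providers trained on VIA/VILI and cryotherapy", which describes skills and not equipment.

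On the intervention side, Potential Benefits states "The selected reproductive health clinics will receive thermal ablation equipment". The Training phase adds hands-on TA training, a VIA/VILI refresher, community outreach and quarterly medical education. The Intensive implementation phase adds bi-weekly technical assistance and quarterly county supervision.

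The Outcome Variable paragraph defines the primary outcome as the pre/post change in treatment completion among screen-positive women. The Reach text counts cryotherapy, LEEP or any other procedure towards completion. For effect modifiers, Data analysis says "Exploratory analysis will examine potential effect modification of facility-level factors such as patient volume, patient to provider ratio, and women screened".

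**The concern.** A reader of the hypothesis will take a positive result to mean that TA does better than cryotherapy. Two features of the design stand in the way.

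- The device and the support start together in every clinic. Randomising the order of rollout controls for secular trend, but it cannot separate two components that always switch on at the same time.
- The control condition is whatever each clinic already does. In a clinic without working cryotherapy that is screening with little or no on-site ablation, so the contrast there is not with cryotherapy at all.

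The protocol itself takes the comparison with cryotherapy further. Aim 3 describes prior practice in the costed clinics as SVA-SAT with cryotherapy, and its budget impact model takes reach and effectiveness for each strategy from Aim 2. If control-period results are labelled as cryotherapy results, the label passes to the Ministry of Health analysis. Study Limitations discusses concurrent interventions and contamination, but not the bundling of device and support.

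**Working it through.** **1. What differs between control and intervention time**

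| Element | Control period | After crossover | Source in the protocol |
| --- | --- | --- | --- |
| Ablative device | Whatever the clinic has; no requirement | TA equipment supplied | Human Subjects Considerations; Potential Benefits |
| Training | Some providers already trained in VIA/VILI and cryotherapy | TA training, VIA/VILI refresher, quarterly medical education | Training phase |
| Demand creation | None described | Outreach before on-site training | Training phase |
| Mentoring and supervision | None described | Bi-weekly visits, quarterly supervision | Intensive implementation phase |
| Research contact | Baseline survey, monthly abstraction | Abstraction continues | Baseline data period |

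Outreach comes shortly before the on-site training, so some of it may fall in control time. That does not restore a comparison of devices.

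The outcome does not isolate TA either. Completion counts any procedure. The Power and sample size paragraph words the outcome as same-day ablation, which would count cryotherapy and TA alike.

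**2. The plan's own figures**

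Power and sample size assumes 20% coverage before and 60% after, so 60 − 20 = 40 points. The 20% is a Kiambu County figure for 2017–2019 that combines cryotherapy and LEEP. It is not the performance of working cryotherapy in the ten clinics.

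The stated power is 80%. A simple stepped-wedge weighted least squares model does not give that figure. Its inputs are four periods, 3/3/4 clinics, 9 women per clinic-period, ICC 0.2 and two-sided alpha 0.05:

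- Residual variance (0.16 + 0.24)/2 = 0.20; between-clinic variance 0.2 × 0.20/0.8 = 0.05.
- Standard error 0.0868; 0.40/0.0868 − 1.96 = 2.65; power 99.6%.

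The protocol also mentions random effects per facility and wave but gives no variances. Suppose half the between-clinic variance is a clinic-by-period component and the treatment effect has variance 0.05 (both assumptions). The standard error is then 0.1408, and power is 81.1%. So 80% is attainable and is not shown to be wrong. The present point does not depend on it, because no sample size separates the device from support that starts with it.

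**3. How far the 40 points could differ from a TA-versus-cryotherapy contrast**

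The documents supply no input for this, so both calculations are illustrations.

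(a) *Missing cryotherapy.* Let a fraction f of clinics have no working cryotherapy and treat nobody. Assume equal numbers of screen-positive women per clinic, the overall control rate held at 20%, and 60% reached everywhere. Control completion where cryotherapy works is then 20%/(1 − f), and the gap is 60% minus that.

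| f | Control rate with working cryotherapy | Gap to 60% |
| --- | --- | --- |
| 0 | 20% | 40 points |
| 0.2 | 20/0.8 = 25% | 35 points |
| 0.4 | 20/0.6 = 33.3% | 26.7 points |
| 0.5 | 20/0.5 = 40% | 20 points |
| 0.6 | 20/0.4 = 50% | 10 points |

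The zero is the extreme case, since LEEP or another procedure would count towards completion.

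(b) *Support bundled with the device.* If training, outreach and supervision produce 25%, 50% or 75% of the 40 points, the device accounts for 30, 20 or 10 points. This applies even at f = 0. The trial yields no data that could choose among these values.

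**The case against.** The strongest reply is that unreliable cryotherapy is what the trial is about. The Executive Summary attributes low treatment rates to equipment shortage, gas supply and equipment failure. On that view standard of care means cryotherapy as it really exists, failures included, and conditioning on working machines removes the problem under study. This stands in part: existing practice is a legitimate comparator, and device failure or gas shortage belongs to it. But refresher training, outreach and mentoring are not properties of the TA device, and TA equipment is supplied by the study.

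Second, the objective and the pre/post analysis already address package versus usual practice, and bundling is normal in an implementation trial. This stands in full. It confines the problem to the hypothesis sentence and to conclusions drawn from it.

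Third, the evidence on missing equipment is thin. The survey covered 12 potential clinics, no count is given, some providers at the selected clinics are trained in cryotherapy, and the costing section presumes that cryotherapy is standard practice. This also stands. A reader might infer that some of the ten clinics lack cryotherapy, but the documents do not establish it.

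Fourth, equipment is recorded at baseline, the list of modifiers is open-ended, and a statistical analysis plan may extend it. So leaving cryotherapy status off the list is not in itself an error. Naming it is a low-cost improvement.

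Two stronger readings should be resisted. A reader might infer that the primary analysis is invalid. It is not, because it answers the package question. A reader might also infer that TA can be compared with cryotherapy in the clinics where cryotherapy works. There too, supported TA is set against unsupported cryotherapy, so the support remains confounded with the device.

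**Conclusion.** The point holds as a mismatch between the hypothesis and the design. The trial can support a statement that the SVA-SAT+TA implementation package changes treatment completion relative to existing practice. It cannot attribute that change to TA over cryotherapy.

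The bundling follows directly from the protocol text and needs no assumption. The contribution of missing cryotherapy rests on the screening-only eligibility statement and on the implication that equipment was not universal among the surveyed clinics. Its size is unknown. Under the illustrative assumptions above, the gap against working cryotherapy runs from the full 40 points when every clinic has it to 10 points when 60% have none. Those values show sensitivity and are not estimates. The correction should be made, because it governs what the trial may claim, but it requires no change to the design or the primary analysis.

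**What to change.** - Restate the hypothesis in the Executive Summary, and the conclusions that follow from it, as a comparison of *the SVA-SAT+TA implementation package versus existing practice, with or without working cryotherapy*. Use the same description wherever Aim 2 control-period results enter Aim 3.
- In Data analysis, add working cryotherapy at the clinic (yes/no) as a pre-specified exploratory modifier. Take it from the baseline equipment data and update it at the monthly abstraction.
- Report control-period completion and the effect descriptively by that status.
- State that no TA-versus-cryotherapy device claim will be made in either subgroup, because support is confounded with the device in both.

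The cost is revised wording, one yes/no item at abstraction and one exploratory table. The headline claim becomes narrower. The split will be imprecise: there are only ten clinics over three steps, and randomisation is stratified by size and not by cryotherapy status, so a subgroup may be unevenly spread across steps.
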